## Abstract

**Background:**

Chronic obstructive pulmonary disease (COPD) is significantly underdiagnosed in Kazakhstan, and there is no previously conducted study on COPD prevalence in the country.

**Objective:**

The purpose of this study is to assess the prevalence of COPD among individuals aged 40 to 59 years based on results of spirometry before and after bronchodilator, presence of structural changes in the lungs (emphysema, inflammatory changes, and thickening of the walls of the large and small airways) detected by computer tomography, and the symptoms of COPD. The study has 3 study groups: smokers of conventional cigarettes, those who had quit smoking 1 to 5 years ago, and those who haven’t smoked cigarettes.

**Methods:**

This is an observational study with a cross-sectional design among individuals aged 40 to 59 years in Almaty, Kazakhstan. The sample of 900 individuals of both sexes contains 500 smokers, 200 ex-smokers, and 200 never-smokers. Study measures include spirometry, chest computed tomography, electrocardiography, physical exams, laboratory testing of serum, anthropometry, and 6-minute walk test. Data are collected by computer-assisted personal interviewing with tablets. The questionnaire was designed to explore possible COPD risk factors including history of smoking, current smoking, level of smoking exposure (in pack-years), passive smoking, occupational and environmental hazards, and covariates: age, gender, ethnicity, education, occupation, and self-reported morbidity. COPD Assessment Test (CAT) is used to collect information about COPD symptoms.

**Results:**

We have completed the participant recruitment and study procedures. Currently, we are working on data processing and data analysis. The authors anticipate the preliminary results should be available by September 2017. Study results will be published in peer-reviewed scientific journals.

**Conclusions:**

This is the first study in Kazakhstan that assesses prevalence of COPD and its comorbidities in the adult population aged 40 to 59 years. The results of the study will be useful for improving COPD preventive measures, better COPD screening, identification, and registration. Findings of the study will also contribute to global knowledge on the epidemiology of COPD.

**Trial Registration:**

ClinicalTrials.gov NCT02926534; https://clinicaltrials.gov/ct2/show/NCT02926534 (Archived by WebCite at http://www.webcitation.org/6rjwGsPOZ)

## Introduction

Chronic obstructive pulmonary disease (COPD) is the fourth leading cause of death worldwide [1]. The number of affected individuals and deaths from COPD are expected to increase as the population ages [2]. In Russia, the largest neighboring country of Kazakhstan, the prevalence of symptomatic COPD in the adult population was estimated to be 15.3% [3]. An estimated 1.4 million individuals in Kazakhstan may be affected by COPD. This estimate is based on studies that have been conducted in other countries in the World Health Organization European Region [4] but not in Kazakhstan, because a study on the prevalence of COPD has not been conducted in the country yet. COPD is significantly underdiagnosed in Kazakhstan. In 2013, the rate of reported COPD cases was 315.9 per 100,000 or around 53,000 registered cases of COPD [5]. A better understanding of the epidemiology and social and other determinants of the disease is needed in order to recognize the true magnitude of the problem and develop effective treatments and prevention strategies.

Various criteria for COPD have been used in population-based studies. The most common criterion is airflow obstruction detected by spirometry testing, defined as a postbronchodilator ratio of forced expiratory volume in 1 second (FEV_1_) to forced vital capacity (FVC) less than 0.7 or 70% [6]. This criterion is simple to implement and widely used in epidemiological surveys. However, COPD prevalence based on this could be slightly biased—overestimated in old subjects and underestimated in younger ones [7]. For this reason, the fifth percentile of the FEV_1_/FVC ratio or the lower limit of normal distribution of the FEV_1_/FVC ratio defined for specific age-gender group is also recommended for use in epidemiological studies [8].

Respiratory symptoms [9] and physical examination [10] were frequently used to evaluate COPD prevalence. However, collecting such data is more important for establishing the clinical diagnosis of COPD [6]. The specific symptoms of COPD include progressive dyspnea, cough, and sputum production [6]. The COPD Assessment Test (CAT) was specially designed to measure how COPD symptoms lead to health status impairment. The test is derived from 8 items, and the score varies from 0 to 40. The cut-off point for the CAT is 10, after which regular treatment for symptoms is recommended [6]. Although a physical examination is rarely used in COPD diagnosis, particularly in detecting mild to moderate COPD, thoracic examination of patients with severe disease can usually reveal the following signs: hyperinflation, wheezing, diffusely decreased breath sounds, hyperresonance on percussion, and prolonged expiration [11].

Chest computed tomography (CT) scan is recommended for subjects with airflow limitation and signs and symptoms suggestive of COPD for making an accurate diagnosis of COPD to exclude other conditions [12]. CT scan also helps to separate COPD patients into 2 main phenotypes, emphysema and small airway disease [13]. CT images can be visually assessed by qualified observers to describe patterns of altered lung structure or quantified for assessment of the extent of emphysema, gas trapping, and airway abnormality [14]. Some studies suggested that severity of emphysema detected by CT scan is associated with greater lung function decline even if airway obstruction is not currently presented [15,16]. As a result, CT-detected emphysema may predict future development of airflow obstruction [16,17].

Tobacco smoking, occupational and environmental exposures including workplace dusts and chemicals, and smoke from home cooking and heating fuels are the main risk factors for COPD [8]. In addition, advanced age, chronic respiratory infections such as tuberculosis, low socioeconomic status, and being underweight may influence COPD development [18,19]. Genetic predisposition also plays an important role in COPD development. Originally described more than 50 years ago, α_1_-antitrypsin deficiency may cause COPD and accounts for 1% to 2% of all COPD cases. There are other genome variants currently being investigated as candidates for COPD genes, but only the Z variant of α_1_-antitrypsin is accepted as a COPD gene at the present time [20].

Comorbidities are frequently found in persons with COPD. Some of them have risk factors, which are the same as for COPD, particularly tobacco smoking and aging. Moreover, systemic inflammation and chronic hypoxia present in COPD patients may cause other health-related conditions. Common comorbidities include heart disease, lung cancer, osteoporosis, metabolic syndrome and diabetes, anemia, anxiety, cognitive decline, and sleep disorders [21,22]. Specific comorbidities increase mortality and poor outcome in COPD, so management of main comorbidities has been included to COPD guidelines [6].

The aim of the study is to assess the prevalence of COPD among smokers, ex-smokers, and never-smokers aged 40 to 59 years based on pulmonary function assessment (spirometry), structural changes (emphysema and large and small airway inflammation with thickening) identified by high-resolution CT, COPD symptoms, and exercise limitations. In addition, the study objectives include comparing the prevalence of health conditions considered as COPD comorbidities (heart disease, hypertension, metabolic syndrome, diabetes mellitus) in 3 study groups and their interaction with COPD.

## Methods

### Study Design

This is an observational study with a cross-sectional design to assess the prevalence of COPD in Almaty, Kazakhstan, among individuals aged 40 to 59 years based on results of spirometry, the presence of structural changes in the lungs, and symptoms of COPD.

The study population is 3 groups of male and female residents of Almaty, the largest city in Kazakhstan, with a population of 1.7 million people, 9% of whom are aged 40 to 59 years. Members of the first group include current smokers with more than a 10 pack-year history of smoking (smokers). The second group comprises individuals who quit smoking from 1 to 5 years ago and have more than a 10 pack-year history of smoking (ex-smokers). The third group comprises persons who have never smoked regularly (ie, smoked less than 100 cigarettes in their lifetime) (never-smokers).

We recruited individuals who are 40 years of age or older because most people are at least 40 years old when the symptoms of COPD first appear [23]. The same age limit is selected for many COPD prevalence studies [24-26]. The upper age was set at 59 years to avoid survival bias [27] possibly leading to underestimating the effects of risk factors on COPD. We have taken into account that the life expectancy at birth among males was only 66 years in Kazakhstan in 2015 [28].

### Inclusion and Exclusion Criteria

Male and female participants aged 40 to 59 years who have a 10 pack-year and more of smoking history (for smokers and ex-smokers) or fewer than 100 cigarettes in their lifetime (for never-smokers) and are able to provide informed consent can be included in this study.

Exclusion criteria:

PregnancyFever (37°C or higher) at the time of the visit or during the 2 weeks preceding the visitLegally incapableChronic infectious and noninfectious lung disease except asthma (eg, pulmonary fibrosis, bronchiectasis, cystic fibrosis, tuberculosis)Resection of at least one lobe (or performing procedures to reduce lung volume)Any cancer; receiving a course of radiation or chemotherapy at the time of the visitSuspected lung cancer (presence of significant lung neoplasm)Presence of metal in the chestOphthalmic surgery within the last 12 months prior to the visitMyocardial infarction or other form of acute or chronic coronary insufficiency or cardiac arrhythmia diagnosed at least 6 months prior to the visitMyocardial infarction or other form of acute or chronic coronary insufficiency or cardiac arrhythmia for which an individual regularly receives medicationSeverely elevated blood pressure (equal to or greater than a systolic 180 or diastolic of 100)History of cerebrovascular accidentThoracic or abdominal surgery within the last 6 monthsContraindications to use salbutamol or its analogsCT scan or other research using ionizing radiation within the last 6 months

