### Sampling

According to the Burden of Obstructive Lung Disease (BOLD) protocol, a minimal sample size of 600 is recommended to achieve an acceptable level of precision for estimating COPD prevalence [29]. Our goal is for a sample size of 900 including 500 smokers, 200 ex-smokers, and 200 never-smokers. We have used the National Health and Nutrition Examination Surveys data to assume COPD prevalence in these 3 groups [30]. The sample size of 500 allows for achieving the precision of 3.5% with the expected prevalence of obstructive impairment of 20%. The sample size of 200 and the expected prevalence of pulmonary obstruction of 10% and 2% among ex-smokers and never-smokers, respectively, provides sample estimates with 4.2% and 1.9% precision, respectively [31].

The 3 study groups are planned to have the same gender and age distribution by implementing age-gender quota to eliminate age and gender potential confounding effect to the associations between smoking status and outcomes.

It was shown that the sample characteristics depend on recruitment method used [32]. To recruit study participants, active and passive approaches are used. Participants are recruited by using personal networks of investigators and persons who are already participating in the study (snowball), placing an advertisement of the study in social media (Facebook) targeting those individuals who are potentially eligible to participate (live in Almaty, specific age group), and meeting with the owners and managerial staff of several large companies located in Almaty to explain the benefits of participation in the study. Employees of these companies who are potentially eligible to participate in the study are contacted by phone calls.

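### As worded, the lung-disease exclusion covers previously diagnosed COPD, which contradicts the aim of estimating COPD prevalence; on the article's own figures the resulting bias is small

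*Protocol article*

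**What the plan says.** The exclusion list in Inclusion and Exclusion Criteria bars anyone with chronic "infectious and noninfectious lung disease except asthma (eg, pulmonary fibrosis, bronchiectasis, cystic fibrosis" and, last in the list, tuberculosis). The bracketed conditions are given only as examples, and asthma is the single exception. No section of the article exempts COPD, chronic bronchitis or emphysema, and none says outright that diagnosed COPD is excluded.

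The target is stated in the Introduction: "The aim of the study is to assess the prevalence of COPD among smokers, ex-smokers, and never-smokers aged 40 to 59 years". The Abstract and Study Design give the same target.

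The Introduction also describes how much COPD is already known. It says that "the rate of reported COPD cases was 315.9 per 100,000 or around 53,000 registered cases of COPD" in 2013, against an estimated 1.4 million affected people, and it calls the disease heavily underdiagnosed.

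The Discussion lists five limitations: observational design, cross-sectional timing, nonprobability sampling, a single city, and measurement bias. This criterion is not among them.

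**The concern.** COPD is itself a chronic noninfectious lung disease. The authors considered which airway disease to exempt and named only asthma. A screener who follows the text would turn away a volunteer with a COPD diagnosis, and that person would leave both the numerator and the denominator. The estimate would then be the prevalence of COPD not yet diagnosed, reported as the prevalence of COPD.

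Two further consequences follow if that happened:

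- The study is motivated by underdiagnosis, but its sample could not show what share of COPD is already recognised.
- Associations between smoking status and COPD would be distorted if the diagnosed share differs between smoking groups.

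**Working it through.** **Inputs.** From Sampling: smokers n = 500 with expected prevalence 20%; ex-smokers n = 200 with 10%; never-smokers n = 200 with 2%; stated precision 3.5%, 4.2% and 1.9%. From the Introduction: 53,000 registered and 1.4 million estimated cases. Assumed: a 95% two-sided interval for the precision figures, and diagnosed shares of 10%, 20% and 30% to show a range.

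**Step 1: reproduce the stated precision.** Half-width = 1.96 × √(p(1 − p)/n).

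- Smokers: 1.96 × √(0.20 × 0.80/500) = 3.51% (stated 3.5%)
- Ex-smokers: 1.96 × √(0.10 × 0.90/200) = 4.16% (stated 4.2%)
- Never-smokers: 1.96 × √(0.02 × 0.98/200) = 1.94% (stated 1.9%)

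All three agree, so these are suitable yardsticks for the bias.

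**Step 2: effect of removing known cases.** Let k be the share of true cases already diagnosed and therefore excluded. Among those still eligible, the prevalence is p′ = p(1 − k)/(1 − pk), which is below p for any k above 0.

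**Step 3: k from the article.** 53,000/1,400,000 = 3.8%. In samples of the planned size this corresponds to about 3.8 of 100 expected cases in smokers, 0.8 of 20 in ex-smokers and 0.15 of 4 in never-smokers.

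| k | Smokers (20%) | Ex-smokers (10%) | Never-smokers (2%) |
|---|---|---|---|
| 3.8% (article's ratio) | 19.4% (−0.6 points) | 9.7% (−0.3) | 1.93% (−0.07) |
| 10% (assumed) | 18.4% (−1.6) | 9.1% (−0.9) | 1.8% (−0.2) |
| 20% (assumed) | 16.7% (−3.3) | 8.2% (−1.8) | 1.6% (−0.4) |
| 30% (assumed) | 14.9% (−5.1) | 7.2% (−2.8) | 1.4% (−0.6) |

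**Step 4: the share at which bias equals the stated half-width h.** Setting p′ = p − h gives k = h/[p(1 − p + h)].

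- Smokers: 0.035/(0.20 × 0.835) = 21%
- Ex-smokers: 0.042/(0.10 × 0.942) = 45%
- Never-smokers: 0.019/(0.02 × 0.999) = 95%

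**Step 5: group comparisons.** After exclusion the odds in a group are p(1 − k)/(1 − p), so an odds ratio between two groups is multiplied by (1 − k₁)/(1 − k₀). It is unchanged only if the diagnosed shares are equal. With assumed shares of 20% and 5%, the factor is 0.80/0.95 = 0.84.

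**The case against.** The strongest reply is that the authors plainly did not mean to exclude the disease they set out to count. COPD is not named in the criterion. Every example given is a lung disease other than the study outcome, which fits an intent to remove alternative diagnoses. The article is condensed, the recruitment figure is not reproduced, and nothing shows how screeners applied the rule. This stands: the text does not establish that known cases were turned away. It does not remove the contradiction, because the written rule covers COPD and a reader cannot tell which population was measured.

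The second reply is about size. On the only figures in the article, the shift is a small fraction of the stated half-width in every group. This also stands. The 10% to 30% shares have no source in the document, and even at 20% the 3.3-point bias in smokers falls short of 3.5.

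Third, the 3.8% ratio cannot be carried over to this sample with confidence in either direction. It is national and not specific to ages 40 to 59, and its denominator is borrowed from other countries. Heavy smokers attracted to a lung study might be diagnosed more often; a sample under 60 recruited partly through employers might be diagnosed less often. A reader might take 3.8% as a lower bound, but the documents do not support that.

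Finally, the downward direction concerns this criterion alone. Keeping people with asthma could push apparent obstruction upward, and snowball, social-media and employer recruitment could act either way.

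**Conclusion.** The criterion as worded contradicts the study's aim and has to be reconciled with it. If it was applied as written, this rule by itself lowers prevalence in all three groups. At the article's national ratio the loss is about 0.6, 0.3 and 0.07 points, inside the stated precision. In smokers it becomes comparable with sampling error only if roughly one case in five was already diagnosed, and the article gives no such figure for this population. Bias in group comparisons depends on unequal diagnosed shares, which are unknown.

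A reader might infer that known COPD was in fact excluded, that every reported prevalence is materially too low, or that the CT, symptom and comorbidity analyses lost their severe cases. The documents support none of these. Application of the rule is not described, the article's own ratio gives a small effect with about 96% of cases still eligible under this criterion, and no figure ties prior diagnosis to severity. What is established is an unresolved question about what the prevalence estimate refers to.

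**What to change.** Reword the criterion so that COPD, including chronic bronchitis and emphysema, is exempt alongside asthma. Recruitment is complete, so rewording cannot change who was enrolled, but the article reports that data analysis is still under way and the following can be done now:

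- State whether people with known COPD were eligible in practice.
- Tabulate from the screening records, by smoking group, how many were turned away for it.
- If any were, label the outcome prevalence of previously undiagnosed COPD and add the point to the limitations.
- Give an add-back estimate, (cases + excluded known cases)/(enrolled + excluded known cases), only as a sensitivity analysis. Those diagnoses lack study spirometry, so they mix case definitions, and the records would miss people who never came forward.

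The cost is one line of text and one tabulation. The downside is a possibly narrower outcome label.

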#### Six-Minute Walk Test

All study subjects will take a 6-minute walk test to evaluate functional exercise capacity. Investigators assess whether contraindication exists or not. Absolute contraindications are unstable angina and myocardial infarction during the previous month. Relative contraindications are blood pressure more than 180/100 mm Hg and a resting heart rate of more than 120 beats per minute [39]. Subjects with any of the contraindications are referred to the clinical coordinator for a decision about the conduct of the test. Posttest dyspnea is measured using the Borg scale [40].

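### The first cardiac exclusion is dated in the opposite direction to the other dated exclusions, so a recent cardiac diagnosis without regular medication passes both cardiac criteria

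*Protocol article*

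**What the plan says.** The Inclusion and Exclusion Criteria section of the protocol article has two cardiac exclusions covering the same conditions (infarction, other acute or chronic coronary insufficiency, arrhythmia).

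- The first is dated: "coronary insufficiency or cardiac arrhythmia diagnosed at least 6 months prior to the" visit.
- The second is undated and applies when the person takes regular medication for the condition.

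The other dated events in the list look back over a recent period:

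- fever at the visit or in the 2 weeks before it;
- ophthalmic "surgery within the last 12 months prior to the" visit;
- thoracic "or abdominal surgery within the last 6" months;
- CT or "other research using ionizing radiation within the last 6 months".

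The list also excludes contraindications "to use salbutamol or its" analogs, without naming them.

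The Six-Minute Walk Test section gives the test to all subjects and states: "Absolute contraindications are unstable angina and myocardial infarction during the previous month". Anyone with a contraindication goes to the clinical coordinator, who decides whether the test is done. The Objective in the Abstract assesses prevalence "based on results of spirometry before and after bronchodilator", among other measures.

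**The concern.** A diagnosis made at least 6 months before the visit is an old diagnosis. As worded, an unmedicated arrhythmia found years ago excludes a person, while the same arrhythmia found 2 months ago does not. No other dated event in the list works that way, and nothing else in the article restates the cardiac window in the opposite direction.

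Two things are at stake. One is participant safety: the cardiac criteria do not hold back people with a recent, unmedicated diagnosis before spirometry with a bronchodilator and an exercise test. The other is the definition of the enrolled population: a screener who follows the words and a screener who follows the pattern of the list would decide differently about the same person.

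**Working it through.** No sample size, power or event figure enters this point, and the plan gives no figure to reproduce. The check is a logical one: which combinations of time since diagnosis and regular medication do the two cardiac criteria exclude, and does any other rule close the gap?

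**Step 1. The two cardiac criteria under each reading.** The literal reading is the text as it stands. The recency reading is what the line would say if it ran like its neighbours. It is shown for comparison only and is not put forward as the right rule.

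| Time since diagnosis | Regular medication | Literal reading | Recency reading |
|---|---|---|---|
| 6 months or more | yes | excluded (both criteria) | excluded (second criterion) |
| 6 months or more | no | excluded (first criterion) | not excluded |
| under 6 months | yes | excluded (second criterion) | excluded (both criteria) |
| under 6 months | no | **not excluded** | excluded (first criterion) |

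The readings agree for everyone on regular medication. On these two criteria they give opposite answers for unmedicated people, whichever side of 6 months the diagnosis falls.

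**Step 2. Direction of the dated lines.** Fever, ophthalmic surgery, thoracic or abdominal surgery and ionizing radiation all exclude an event because it is recent. The first cardiac line is the only dated event line that excludes because the event is not recent.

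**Step 3. What else could catch the group in the last row.**

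| Rule | What it may catch | What it leaves |
|---|---|---|
| Salbutamol contraindications | some cardiac conditions, depending on what is counted | conditions are not listed; no time window |
| CT or ionizing radiation in the last 6 months | recent events imaged with radiation | events worked up without it |
| Thoracic surgery in the last 6 months | recent events treated surgically | all others |
| Walk-test contraindications | unstable angina; infarction in the previous month; resting heart rate above 120 | infarction 1 to 6 months old; recent arrhythmia without a raised heart rate; applies to the walk test only, by referral for a decision |

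Each is a partial screen. Even together they do not amount to a rule on recent cardiac diagnoses. For example, an unmedicated arrhythmia diagnosed 2 months ago, with no radiation imaging, no surgery, a normal resting rate and nothing counted as a salbutamol contraindication, passes every stated rule.

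**The case against.** The strongest reply is that the line means what it says. The same list excludes a past cerebrovascular accident, lobe resection and any cancer with no recency limit, so excluding long-established disease is not out of character. This stands: the removal of older cardiac disease cannot be called an error on the text alone. It does not explain why a recent unmedicated diagnosis should remain eligible.

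Second, the gap is narrower than the cardiac lines alone suggest, because the partial screens in the working apply under either reading. Every subject also has a 12-lead ECG that is read for arrhythmia and interpreted by a cardiologist. This stands too. But the text does not give the order of procedures and Figure 1 is not shown, so it cannot be assumed either that the ECG came first or that nobody was checked before the tests.

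Some stronger readings are tempting but not supported:

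- **That people with recent cardiac events did undergo the procedures.** The article reports no such person and no event.
- **That every participant received a bronchodilator.** The Objective names the test, but the Spirometry section does not say that everyone had the drug. Salbutamol is named only in the exclusion list.
- **That the walk-test section shows recent infarction was expected among those enrolled.** That section also lists blood pressure above 180/100, which the exclusion list already rules out, so its contraindications overlap with conditions enrolled people should not have.
- **That different sites enrolled different people.** The study is in one city and no separate sites are described. The most that can be said is that individual screeners could differ.

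**Conclusion.** The point holds as an inconsistency in a stated eligibility rule. The first cardiac criterion runs against every other dated event in its list and sits awkwardly with the recency-based check for the walk test. Taken literally, it leaves one group outside both cardiac criteria: diagnosed under 6 months ago and not regularly medicated. Partial screens reduce that group by an unknown amount and do not close it.

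The size cannot be given, because the article reports no count of such people. The safety consequence is a possibility that follows from the wording, not a demonstrated harm. The conclusion assumes that the printed criterion is the one used at screening. If another window was applied, the fault lies in the published text, and the eligible population is misdescribed.

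This is not a matter of detail left out by a condensed article: the criterion is stated in full, and its direction is what conflicts.

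**What to change.** - Reconcile the first cardiac criterion with the neighbouring dated exclusions and with the Six-Minute Walk Test section. Direction, period and any difference between procedures are clinical content for the clinical lead; none is proposed here. If excluding older disease was intended, say so, and say how recent unmedicated diagnoses were handled.
- Recruitment and procedures are complete, so rewording alone protects nobody. State in the results paper which window was actually applied at screening.
- From existing screening records and the self-reported morbidity data, report how many people's eligibility differs between the two readings (the two unmedicated rows in the working), and any events during spirometry or the walk test. Those enrolled and those screened out should be counted separately, since each reading removes a different group.

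The cost is a short clarification and one tabulation of data already held, with no new procedure. The tabulation depends on diagnosis dates and medication having been recorded, which the article does not state. If they were not, the sponsor should say so, and the number stays unknown.
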